## ***4.2 Special safety-related procedures/******instructions for rapid notification of SAEs***

To ensure patient safety all SAEs must be reported by the investigator to the Ethics committee within 24 hours of learning of its occurrence, even if it is not felt to be treatment related. Follow-up information about a previously reported SAE must also be reported by the investigators. SAE reports should be forwarded to:

Secretary

Data Safety Monitoring Sub Committee

Tata Memorial Hospital, Mumbai

# **5. Statistical Analysis**

5.1 SAMPLE SIZE CALCULATION: The primary outcome (difference in VAS at baseline and 9 weeks) will used to determine effect size. Sample size will be calculated assuming an effect size of 0.5, with a type I error rate of 5% and power of 80%.

t tests - Means: Difference between two independent means (two groups)

**Input:** Tail(s) = Two

Effect size d = 0.5

α error prob = 0.05

Power (1-β error prob) = 0.80

Allocation ratio N2/N1 = 1

**Output:** Noncentrality parameter δ = 2.828427

Critical t 1.978971

Df = 126

Sample size group A = 64

Sample size group A = 64

Total sample size = 128

Actual power = 0.801460

We will account for a 30% lost-to-follow-up given the fact that a large proportion of patients will have advanced lung cancer. Therefore, the final estimated sample size will be 166.

5.2 STATISTICAL TESTS:

Data will be entered and analyzed using an appropriate statistical program, like SPSS software, version 20 (IBM SPSS Statistics for Windows, Version 20.0. Armonk, NY: IBM Corp.) and R Project for Statistical Computing, version 3.5.1[R Core Team (2013). R: A language and environment for statistical computing. R Foundation for Statistical Computing, Vienna, Austria, URL <http://www.R-project.org/>]*.* Baseline characteristics including demographic data, treatment details, details of the diagnosis and adverse events will be represented as simple percentages.

Statistical Analysis will be done as per intention to treat and per protocol principle. All patients with a complete cough severity assessment at baseline and on 9 weeks will be included for analysis. Patients without any follow-up information after randomization will be excluded. We will use complete-case analysis to handle missing data, i.e. the missing observations will be excluded from the analysis.

To measure cough severity, the VAS score at 9 weeks will be subtracted from the baseline score. The means of the change from the baseline scores will be calculated for all patients in each arm and the means will be compared between the two arms using two-sided Student’s t-test. A *P* value of <0.05 will be considered significant. The effect size will be determined with the use of Cohen’s d statistic, which is a measure of the difference between two means divided by an estimate of a pooled standard deviation. As per conventional classification, an effect size of 0.2 will be considered small, 0.5 moderate, and 0.8 large (19). A similar methodology will be used to evaluate the cough impact using the MCLCS. The change in the VAS scores and MCLCS scores from baseline to day 7 to 9 weeks and will be explored graphically between the arms.

QoL data will be scored as per the procedure described in the EORTC scoring manual (15,16). Different subdomain wise QoL data will be generated from the QoL dataset. A subdomain wise comparison was performed between the arms, using the linear mixed effect model.

The difference in toxicities between the two arms will be compared using the Pearson chi-square test or Fisher Exact test.

**6. Feasibility of the Study:** We see approximately 1300 lung cancer patients in a year at Tata Memorial Hospital. We expect to complete the study within 24 months of approval of study.

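### The 166 patients do not cover the 30% loss allowed for: about 116 would remain of the 128 needed, and power would be about 76%, not 80%

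*Protocol*

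**What the plan says.** Section 5.1 bases the sample size on the change in cough VAS from baseline to 9 weeks, compared between two independent groups with a two-sided t-test. The inputs are printed as "Effect size d = 0.5", "α error prob = 0.05", "Power (1-β error prob) = 0.80" and "Allocation ratio N2/N1 = 1". The output is "Total sample size = 128", which is 64 per arm with an actual power of 0.801460.

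The section then turns to attrition: "We will account for a 30% lost-to-follow-up given the fact that a large proportion of patients will have advanced lung cancer". The next sentence draws the conclusion: "Therefore, the final estimated sample size will be 166". The synopsis repeats 166. The formula that leads from 128 to 166 is not printed.

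Section 5.2 fixes how lost patients are treated. Only patients with cough severity assessed both at baseline and at 9 weeks enter the analysis, and missing observations are dropped (complete-case analysis). For the primary outcome, "the means will be compared between the two arms using two-sided Student’s t-test".

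**The concern.** The 128 patients are the number the t-test must analyse to reach 80% power. If 30% of those randomised are lost, the number randomised has to be 128 divided by the 70% who remain. Adding 30% of 128 gives a smaller number, and 30% of that larger total is then lost, so the remainder falls below 128.

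The attrition sentence reads as a promise that the 80% power survives a 30% loss. If it does not, the main design claim is wrong under the plan's own assumption, and a non-significant primary result would be read against a power the trial did not have. The complete-case rule carries the shortfall straight into the primary test, because the specified analysis recovers no information from patients without a 9-week score.

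**Working it through.** **Inputs, all from sections 5.1 and 5.2 of the protocol:** standardised difference d = 0.5; two-sided α = 0.05; target power 0.80; 1:1 allocation; 128 evaluable patients; 30% loss; 166 randomised; complete-case two-sample t-test.

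**Step 1: reproduce the base figure.** With n per arm, the noncentrality is d × √(n/2) and the degrees of freedom are 2n − 2.

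- n = 64: noncentrality 0.5 × √32 = 2.828; df = 126; critical t = 1.97897; power = 0.80146.

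These agree with the printed noncentrality, critical t, df and power. The 128 is correct.

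**Step 2: reproduce the 166.**

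- 128 × (1 + 0.30) = 166.4, which rounds to 166.
- 128 / (1 − 0.30) = 182.9, which rounds up to 183. With equal arms, 64 / 0.70 = 91.4, so 92 per arm and 184 in total.

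Of these two ways to apply the allowance, only the first gives 166. That this was the route taken is an inference, since the protocol does not show the step. The result in step 3 does not depend on it.

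**Step 3: apply the planned loss to 166.**

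- 166 × 0.70 = 116.2, about 58 per arm, which is 12 fewer than 128.
- n = 58: noncentrality 0.5 × √29 = 2.693; df = 114; critical t = 1.981; power = 0.761.
- The type II error at d = 0.5 is therefore 1 − 0.761 = 0.239, against about 0.20 as designed.
- The difference detectable with 80% power at 58 per arm is d = 0.525.

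**Step 4: the loss that 166 can bear.** 128 of 166 remain evaluable if at most 38/166 = 22.9% are lost.

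**Step 5: power with 166 randomised, by loss (d = 0.5).** Fractional arm sizes are kept, which is why the 30% row shows 0.762 and not 0.761.

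| Loss | Evaluable | Power |
| --- | --- | --- |
| 20% | 132.8 | 0.816 |
| 22.9% | 128.0 | 0.801 |
| 25% | 124.5 | 0.790 |
| 30% | 116.2 | 0.762 |
| 35% | 107.9 | 0.730 |

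**Step 6: check of the alternative.** With 184 randomised and 30% lost, 128.8 remain and power is 0.804.

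**The case against.** The arithmetic is not in dispute. The case on the other side concerns weight and wording.

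- **Size.** The loss is about 4 points of power, and the detectable difference moves only from 0.50 to 0.525. The 0.5 is a conventional moderate effect; section 5.1 does not derive it from a minimal important difference on the VAS. The type I error is unaffected. This stands: the shortfall is moderate and would rarely decide how a result is read.
- **Conditionality.** The shortfall appears only if loss exceeds 22.9%. The protocol gives no data for 30%, entry is limited to performance status 0 to 2, and the endpoint is at 9 weeks, so actual loss could be lower or higher. This also stands, but 30% is the plan's own planning value and the design should be judged against it.
- **What is actually stated.** The protocol attaches 80% power to 128 patients and never prints a power for 166 with 30% lost. That is correct. Still, the purpose of a loss allowance is to preserve the power just calculated, and the word introducing the 166 presents it as following from that allowance.
- **Another reading of the 30%.** It could mean 30% of the evaluable number, which would make 166 consistent. That implies a true loss of 22.9%, which is not what a 30% loss to follow-up ordinarily means: patients are lost from those randomised.
- **Recovery by a better analysis.** Adjusting for baseline in place of the plain change-score t-test could offset the shortfall. With equal variances at the two times, adjustment multiplies the variance by (1 + ρ)/2, where ρ is the correlation between baseline and week-9 VAS. Making 116 patients worth 128 needs (1 + ρ)/2 ≤ 116/128 = 0.906, so ρ below about 0.81. Power at 58 per arm would be about 87% at ρ = 0.5 and about 78% at ρ = 0.9. The protocol gives no ρ and does not specify this analysis, so recovery is plausible but cannot be claimed as it stands.

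**Conclusion.** The concern holds. The calculation of 128 is correct, but 166 does not provide for a 30% loss. At that loss about 116 patients are analysed and power for d = 0.5 is 76.1%, about 4 points below the 80% intended. The same 80% would apply to d = 0.525. The design reaches its target only if no more than 22.9% are lost.

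This rests on the protocol's own inputs and on three conditions: the 30% refers to patients randomised, losses are about equal between arms, and the primary analysis is the complete-case t-test of section 5.2. The effect is moderate, but the sample size statement is wrong as written and should be corrected.

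**What to change.** Keep 166 and replace the last two sentences of section 5.1 with a statement such as: *166 randomised patients give 80% power for d = 0.5 if at most 23% are not evaluable at 9 weeks; with 30% loss (116 evaluable) power is 76% for d = 0.5, or 80% for d = 0.525.* The synopsis figure of 166 then stands unchanged. The cost is one sentence and a slightly less favourable power figure; no patients are added and nothing in the conduct of the trial changes.

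If 80% power at 30% loss is to be kept, the alternative is to randomise 184 patients (92 per arm), 18 more than now, and to change the number in the synopsis as well. If the sponsor prefers to rely on a baseline-adjusted analysis to make up the shortfall, section 5.2 must name it as the primary analysis and section 5.1 must state the assumed correlation.

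### The analysis labelled intention to treat is a week-9 completer analysis, with about 30% of randomised patients expected to be lost

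*Protocol*

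**What the plan says.** Section 5.2 first names the principle: "Statistical Analysis will be done as per intention to treat and per protocol principle". It then defines who is analysed: "All patients with a complete cough severity assessment at baseline and on 9 weeks will be included for analysis". A separate exclusion comes after that: "Patients without any follow-up information after randomization will be excluded". The treatment of gaps in the data is fixed in the same paragraph: "We will use complete-case analysis to handle missing data, i.e. the missing observations will be excluded from the analysis".

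The primary test, also in Section 5.2, is a two-sided t-test on the change in VAS from baseline to week 9. A linear mixed-effects model is named only for the quality-of-life data.

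Section 5.1 states how much loss is expected and why: "We will account for a 30% lost-to-follow-up given the fact that a large proportion of patients will have advanced lung cancer". Section 3.6 schedules the VAS at baseline, day 7 and week 9, so an intermediate measurement exists. The primary analysis does not use it.

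**The concern.** Membership of the primary analysis set depends on something that happens after randomisation, namely reaching and completing the week-9 assessment. That conflicts with the ITT label. The protocol fixes the set, the missing-data method and the test itself, so a later SAP that followed it would inherit the conflict.

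The text is also unclear about one group. The exclusion of patients with no follow-up at all is redundant once week-9 data are required, so it is not obvious what the authors intended for patients who have a day-7 score but no week-9 score. Read as written, they are dropped.

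What is at stake is the protection given by randomisation. The protocol's section on cancer-directed therapy relies on randomisation to balance tumour response between arms, and selecting on week-9 completion weakens that reliance. Patients lost to advancing disease probably have worse cough than those who stay. If that selection differs between arms, the estimated effect shifts, in either direction.

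**Working it through.** **Inputs from the protocol.** Section 5.1: effect size 0.5, two-sided 5% error, 80% power, equal arms, 64 per arm (128 in total), 30% loss, 166 randomised. Section 3.6: VAS at baseline, day 7 and week 9.

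**Inputs assumed, because the protocol gives none.** VAS SD 25 mm at each visit; correlations 0.5 (baseline with day 7), 0.4 (baseline with week 9) and 0.6 (day 7 with week 9); true week-9 effect 0.5 × 25 = 12.5 mm, or zero; 83 patients per arm; about 30% loss per arm.

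**Step 1. Reproduce the plan's figures.** Noncentrality = 0.5 × √(64/2) = 2.828; critical t on 126 df = 1.979; power = 0.8015. All agree with Section 5.1. Inflation: 128 × 1.30 = 166.4, matching the stated 166.

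**Step 2. Who is left.** 166 × 0.30 = 49.8, so about 50 randomised patients leave the primary comparison. 166 × 0.70 = 116.2, so about 116 (58 per arm) remain.

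**Step 3. When this biases the comparison.** Let p be the share lost in an arm, c the completers' mean improvement, and g the amount by which lost patients improve less than completers. The mean over all randomised patients is (1 − p)c + p(c − g) = c − pg, so completers overstate an arm's improvement by pg. The bias of the between-arm difference is therefore

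pA·gA − pB·gB (A = pregabalin, B = placebo; positive favours pregabalin).

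In SD units, with the rejection rate of a nominal 5% test at 58 per arm when there is no true effect:

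| Loss A / B | Gap A / B (SD) | Bias (SD) | Rejection rate |
|---|---|---|---|
| 30% / 30% | equal | 0 | 5% |
| 35% / 25% | 0.5 / 0.5 | 0.05 | about 6% |
| 35% / 25% | 1 / 1 | 0.10 | about 8% |
| 30% / 30% | 1 / 0.5 | 0.15 | about 13% |
| 40% / 20% | 1 / 1 | 0.20 | about 19% |

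The loss rates and gaps are illustrations. Equal loss with an equal gap gives no bias at all, however large the loss.

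**Step 4. The same question in millimetres, by simulation.** The SD of change under the assumed values is 25 × √(2 × (1 − 0.4)) = 27.4 mm, so 0.20 SD is about 5.5 mm.

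| Dropout mechanism | True effect | Complete case | Model using day 7 |
|---|---|---|---|
| Same in both arms | 12.5 mm | 11.8 to 12.7 mm | 12.5 mm |
| Follows day-7 response, placebo only, strong | 12.5 mm | about 6.8 mm | 12.5 mm |
| As above | 0 | about 5.7 mm against pregabalin | about 0 |
| As above, half as strong | 12.5 mm | about 8.9 mm | no bias expected |
| As above, half as strong | 0 | about 3.4 mm against pregabalin | no bias expected |
| Follows week-9 change, placebo only | either | bias about 9.5 mm | bias about 5 mm |

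The 11.8 to 12.7 mm in the first row spans separate simulation runs. The model does well in the day-7 rows by construction, since there loss depends on exactly what the model conditions on. The last row shows what happens when it does not.

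**Step 5. Cross-check with Step 3.** If selection acts in placebo only, at 30% loss, a bias of 5.7 mm implies a gap of 5.7 / 0.30 = 19 mm between lost and retained placebo patients, or 19 / 27.4 = 0.69 SD. The half-strength case implies 3.4 / 0.30 = 11.3 mm, or 0.41 SD. A mechanism giving about 6 mm has roughly 70–77% of the worst fifth of placebo day-7 responders leaving and 2–4% of the best fifth. That is strong selection.

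**The case against.** The best defence is that the one reason the protocol gives for loss, advanced lung cancer, applies to both arms alike, and under a common mechanism the bias is at most about 12.5 − 11.8 = 0.7 mm. The design also works against arm-specific dropout: patients and staff are blinded, intolerable side effects lead to dose reduction rather than withdrawal, and additional cough medicines are available in both arms. This stands as a limit on the size of the problem. It does not rule out differential loss, and it does not repair the label.

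Four stronger readings are tempting, and the document does not support them.

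- **That the result will be biased, or biased against pregabalin.** Loss through side effects on pregabalin or lack of relief on placebo is a plausible inference. Section 3.6 does cite more dizziness and cognitive change on pregabalin in an earlier study, but the protocol nowhere says that these will drive dropout.
- **That toxicity is compared only in week-9 completers.** The restriction is worded for cough assessments, the complete-case rule removes missing observations, and the synopsis and Section 4 have toxicity collected at every visit and all adverse events recorded. A safety population is commonly left to the SAP.
- **That an incomplete MCLCS removes a patient with a valid VAS.** Section 3.6 lists both instruments as cough-severity tools, but Section 5.2 measures severity by VAS and impact by MCLCS. This is loose wording, not an exclusion rule.
- **That a mixed model would be unbiased.** Day 7 falls just as dose escalation ends, and progression or death over the following eight weeks is not captured by it.

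**Conclusion.** The point holds in this form: the primary comparison is called intention to treat but is fixed as a completer analysis, leaving out about 50 of 166 randomised patients at the loss the protocol itself predicts. This follows from stated rules, not from missing detail.

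The bias is a risk of unknown direction and size. On the assumed SD, correlations and 30% loss, it is near zero if dropout works alike in both arms and about 3 to 6 mm if loss follows day-7 response in one arm only. The upper figure is close to half of the assumed 12.5 mm effect, but it needs strong one-sided selection. Differential dropout is an assumption of this review, not a statement in the protocol.

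**What to change.** 1. Make the primary analysis a longitudinal mixed model of VAS at day 7 and week 9, in all randomised patients with any post-baseline VAS, analysed as randomised. Include baseline VAS, arm, visit and arm-by-visit, and take the week-9 contrast as the primary test.
2. Keep the t-test on complete cases as a sensitivity analysis and call it a completer analysis.
3. Add one sensitivity analysis for loss through death or deterioration, for example one that worsens the unobserved week-9 scores by a stated amount in each arm.
4. Report by arm how many randomised patients contribute to each analysis and how many have no post-baseline VAS, since the model cannot use the latter.

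The cost is revised wording and modest programming. No visit or patient is added: day-7 VAS is already collected, and a linear mixed model is already planned for quality of life. The downside is reliance on data being missing at random given baseline and day 7. That is a weaker assumption than complete-case analysis needs, but it still fails if loss follows later deterioration, which is why item 3 is needed.

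### The primary VAS test is a valid but unadjusted t-test on change; adjusting for the baseline VAS already collected would add precision unless the baseline slope is close to 1

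*Protocol*

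**What the plan says.** Protocol section 5.2 defines the outcome as baseline VAS minus 9-week VAS and then states: "The means of the change from the baseline scores will be calculated for all patients in each arm and the means will be compared" with a two-sided Student's t-test at the 5% level. No covariate is named. Cohen's d is to be reported as the effect size, and MCLCS is to be analysed by a similar method. For quality of life, the same section already plans a linear mixed effect model.

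Section 5.1 sizes the trial on the matching unadjusted two-sample t-test, with "Effect size d = 0.5", "α error prob = 0.05" (two-sided) and "Power (1-β error prob) = 0.80". It ties the effect size to the change in VAS: "The primary outcome (difference in VAS at baseline and 9 weeks) will used to determine effect size". The result is "Total sample size = 128", raised to 166 for 30% loss to follow-up. Missing observations are dropped (complete-case analysis, section 5.2).

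Section 3.6 schedules VAS and MCLCS at baseline, day 7 and 9 weeks. Section 3.4 uses no stratification factors. Section 3.2 restricts entry to CTCAE grade 2 or 3 cough.

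**The concern.** A change score subtracts the baseline value with a fixed slope of 1. ANCOVA estimates that slope from the data. If the true slope is not 1, the change score keeps variance that the baseline measurement could have removed, and in any one trial a chance difference in baseline cough between arms moves the estimate. Nothing in the design balances baseline cough, since randomization is unstratified.

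What is at stake is precision on the primary endpoint and on MCLCS. The loss matters more than usual here because, at the attrition the protocol itself expects, the planned t-test falls short of its 80% target.

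**Working it through.** **Inputs from the protocol (sections 5.1 and 5.2).** Two-sided alpha 0.05; d = 0.5, read as the difference in mean change divided by the SD of change; "Allocation ratio N2/N1 = 1"; 64 per arm evaluable; stated power 0.801460; 166 randomized; 30% loss; complete-case analysis, so lost patients contribute nothing.

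**Inputs not in the protocol (assumed).** The correlation ρ between baseline and week-9 VAS, taken as 0.3 to 0.7, and k = week-9 SD / baseline SD, taken as 0.75 to 1.5.

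**Step 1: reproduce the stated power.** Noncentrality = d√(n/2) = 0.5 × √32 = 2.828427; df 126; critical t 1.978971; power 0.80146. All agree with section 5.1.

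**Step 2: planned test at 30% loss.** 166 × 0.7 = 116.2, so 58 per arm. Noncentrality = 0.5 × √29 = 2.6926; df 114; critical t 1.9810; power **0.761**.

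**Step 3: compare the variances.** With baseline SD s:
- Var(change) = s²(1 + k² − 2ρk)
- Var(ANCOVA residual) = s²k²(1 − ρ²)
- Difference = s²(1 − ρk)²

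The difference is never negative. It is zero only when the slope ρk equals 1. So the condition for a gain is a slope different from 1, not merely a correlation below 1. With equal SDs (k = 1) the variance ratio simplifies to (1 + ρ)/2, which is a reduction of 35%, 25% and 15% at ρ = 0.3, 0.5 and 0.7.

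**Step 4: ANCOVA power at 58 per arm.** Effective d = 0.5/√(variance ratio), df 113. Each cell shows the variance ratio, then power.

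| k | ρ = 0.3 | ρ = 0.5 | ρ = 0.7 |
| --- | --- | --- | --- |
| 0.75 | 0.460; 0.9759 | 0.519; 0.9595 | 0.560; 0.9461 |
| 1 | 0.650; 0.9117 | 0.750; 0.8692 | 0.850; 0.8253 |
| 1.25 | 0.784; 0.8541 | 0.893; 0.8066 | 0.981; 0.7690 |
| 1.5 | 0.871; 0.8160 | 0.964; 0.7760 | 0.998; 0.7619 |

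Example for k = 1, ρ = 0.5: ratio (1 + 0.5)/2 = 0.75; effective d = 0.5/√0.75 = 0.5774; power 0.869.

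**Step 5: where 80% is reached.** The variance ratio must be no more than about 0.908. With equal SDs, (1 + ρ)/2 = 0.908 gives ρ of about 0.82. Power is 0.8035 at ρ = 0.8, 0.7927 at 0.85 and 0.7820 at 0.9.

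**Step 6: a case with no gain.** k = 1.25 and ρ = 0.8 give a slope of 1.25 × 0.8 = 1, a variance ratio of 1 and power of 0.761, the same as the t-test.

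**Step 7: other reading of d.** If d = 0.5 were on the week-9 SD (equal SDs), power at 58 per arm would go from 0.617 to 0.799 at ρ = 0.3, from 0.761 to 0.869 at ρ = 0.5, and from 0.931 to 0.962 at ρ = 0.7. The direction is unchanged. The wording of section 5.1 favours the change scale used above.

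**The case against.** The planned analysis is valid. Randomization makes the change-score t-test unbiased, its standard error already allows for chance baseline imbalance, and the sample-size method matches the test. At 128 evaluable patients it has its stated 80.1% power. All of this stands, so the point concerns efficiency and not an error in the test.

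A reader might infer that adjustment is certain to bring power above 80% at 30% loss. The documents do not support that, because they give neither the correlation nor the SDs. With equal SDs the statement fails above a correlation of about 0.82. It also fails at moderate correlations if week-9 VAS is more spread out (76.9% at k = 1.25, ρ = 0.7; 77.6% at k = 1.5, ρ = 0.5). Wider spread at week 9 is plausible, since restricting entry to grade 2 or 3 cough may narrow the baseline spread. The protocol does not settle whether k is above or below 1.

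A reader might also infer that selecting patients with bad cough biases the comparison through regression to the mean. It does not: selection precedes randomization and applies equally to both arms, so the expected regression is the same in each.

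Finally, the 76% comes partly from another problem. 128 × 1.3 = 166.4, whereas 128/0.7 = 182.9, so 183 would be needed; 166 covers a loss of only 1 − 128/166 = 22.9%. Adjustment may offset some of that shortfall but does not correct it.

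The reply that a separate SAP could supply the covariate is weak, because section 5.2 names the primary test outright.

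**Conclusion.** The point holds as an avoidable loss of precision. Apart from one degree of freedom, ANCOVA cannot do worse than the change score at any correlation or SD ratio, so the direction needs no outside figure. The size does. At 116 evaluable patients and d = 0.5 on the SD of change, the t-test's 76% would become about 83% to 91% for correlations of 0.3 to 0.7 with similar SDs. It would be about 95% to 98% at an SD ratio of 0.75, 77% to 85% at 1.25, and 76% to 82% at 1.5. The change is worth making because it uses a measurement every patient already provides; the trial's validity does not depend on it.

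**What to change.** In section 5.2, make the primary analysis an ANCOVA of week-9 VAS (or change) on arm plus baseline VAS, and report the adjusted difference in mm with its 95% CI. With baseline in the model, both choices of outcome give the same arm effect apart from sign. The protocol computes change as baseline minus week 9, so the text should state which sign favours pregabalin. Specify the same analysis for MCLCS with its own baseline score. Keep the unadjusted t-test and Cohen's d as supportive.

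The cost is a protocol amendment, made before unblinding. No extra data are needed: baseline VAS and MCLCS are already scheduled, and the complete-case rule already requires a baseline cough assessment. The inflation from 128 to 166 should be dealt with separately.
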